### Sample Size Calculation

The significance level alpha is defined as 0.05 (two-tailed) for detecting a mean difference between groups on the primary outcome being the Dexterity Questionnaire 24 (DextQ-24) (4) in favor of the real iTBS-VBT dexterity group. Based on previously observed data one may assume a within-group standard deviation of up to 10 points. The study is designed to detect a mean difference of 10 or more points, which exceeds the MDC95 of 8 points found in our validation study (4). A total sample size of 30 evaluable subjects, 15 per group, is required to detect a mean difference of an at least 1.1-fold within-group standard deviation with a target power of at least 80%. Considering a maximal drop-out rate of 15%, we aim to recruit 36 patients in total.

In any case, patients who do not complete the training sessions and/or even decide to drop out of the study for whatever reason will be encouraged to continue to participate in the scheduled assessments for at least T1 (and/or a time point prior to the individual end of the study) and ideally to provide a postbaseline assessment for at least the primary endpoint.

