### Statistical Analysis

Descriptive statistics are used to present baseline characteristics and results of outcome measurements. In order to investigate the treatment effect for the primary endpoint, a hierarchical testing strategy is applied. For DextQ-24 at T1, an ANCOVA model is used with a fixed effect for treatment and the baseline (T0) value of DextQ-24 as a covariate. If a treatment effect at T1 could have been shown (null hypothesis rejected), the same approach will be performed for DextQ-24 at T2 in order to see whether the treatment effect is sustainable. An estimate for the treatment effect will be derived from the model together with a corresponding 95% confidence interval. As a postestimation procedure effect size measures such as (partial) eta square with corresponding 95% intervals will be provided. In an exploratory manner, the secondary endpoints are tested utilizing the same methodology. As a sensitivity analysis, e.g., to explore the robustness of the results in case of missing values, the primary and secondary endpoints are analyzed using linear mixed effects models with fixed effects for treatment, time point, interaction of treatment and time point, baseline value as a covariate and with subject as a random effect. Estimates for the treatment effects at T1 and T2 with corresponding 95% confidence intervals can be obtained as contrasts derived from these models. Further supportive analyses to check the robustness of the treatment effect estimators can be performed by adjusting the model from the primary analysis for the stratifying variable, namely the H&Y scale.

According to the treatment policy strategy (Intention to treat (ITT) principle) every randomized PD patient, including the drop-outs, is included for final evaluation. For all analyses the level of significance is set to alpha = 0.05 (two-tailed). Statistical analyses are performed using Stata (Version 16.1 or later, StataCorp, College Station, Texas, USA).

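### The plan promises an evaluation of every randomized patient, but its confirmatory ANCOVAs give an available-case estimate, with the greatest exposure at T2

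*Protocol article*

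**What the plan says.** In the protocol article, the Statistical Analysis section sets the confirmatory test: "For DextQ-24 at T1, an ANCOVA model is used with a fixed effect for treatment and the baseline (T0) value of DextQ-24 as a covariate". When that null hypothesis is rejected, "the same approach will be performed for DextQ-24 at T2 in order to see whether the treatment effect is sustainable". No imputation or other rule is given for a patient who lacks the outcome in either model.

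Missing values are mentioned once, for a different model: "As a sensitivity analysis, e.g., to explore the robustness of the results in case of missing values", a linear mixed model is fitted with "fixed effects for treatment, time point, interaction of treatment and time point, baseline value as a covariate and with subject as a random effect".

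The same section then states that, under the treatment policy strategy, "every randomized PD patient, including the drop-outs, is included for final evaluation".

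The Sample Size Calculation section bears on this in two ways. It sizes the trial on patients with usable data: "A total sample size of 30 evaluable subjects, 15 per group, is required", raised to 36 recruited for a drop-out rate of at most 15%. It also provides for retention: patients who stop training or withdraw "will be encouraged to continue to participate in the scheduled assessments for at least T1". The Discussion says that the long follow-up may cause some drop-outs and expects a rate of no more than 10%.

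**The concern.** An ANCOVA has one outcome per patient. A patient without DextQ-24 at T1 is not in the T1 model, and a patient without it at T2 is not in the T2 model. The analysis set that is promised and the model that is to deliver it therefore agree only if no value is missing, and the sample size section plans for some to be missing.

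This is more than a detail left for later. The article does say where missing values are to be addressed, and it places that work outside the confirmatory analysis. The primary estimate, p-value and confidence interval would then be reported as treatment policy for all randomized patients when they describe those with a value at the visit. If the losses relate to response and differ by arm, the estimate is biased. The T2 test carries the claim of a lasting effect, and it is where losses are expected and the retention effort is weakest.

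**Working it through.** **1. The plan's own figures.** Inputs from Sample Size Calculation: standardized difference 1.1, two-sided alpha 0.05, power at least 80%, drop-out 15%. A two-sample t-test (noncentral t) needs 15 per group, with power 0.828. Inflation: 30 / 0.85 = 35.3, rounded up to 36. Both stated figures reproduce. The step from 30 to 36 is needed only if patients without a value are expected to be lost from the analysis.

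**2. How many could be absent.** At 15%: 36 × 0.15 = 5.4, so 5 to 6 patients. At the Discussion's 10%: 36 × 0.10 = 3.6, so 3 to 4. These are upper figures, since drop-outs who still attend the visit stay in the model.

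**3. Who enters each model.** Illustrative data set (counts assumed): 36 randomized, 3 with no post-baseline value, 2 more with T1 but not T2.

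| Model | Status in the plan | Patients used |
|---|---|---|
| ANCOVA at T1 | confirmatory | 36 − 3 = 33 |
| ANCOVA at T2 | confirmatory, second | 36 − 3 − 2 = 31 |
| Mixed model, T0 as covariate | sensitivity | 33 (33 + 31 = 64 rows) |

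Neither model uses all 36. The mixed model keeps the two patients with T1 only. It cannot keep the three with T0 only, because T0 is a covariate and they have no outcome row.

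**4. Loss at T2 after a T1 value.** Assumed inputs: 18 per arm, SD 10, correlation 0.6 between T0 and each follow-up and 0.7 between T1 and T2, true benefit 10 points, and the three real-arm patients with the worst T1 scores missing at T2. Mean estimates over repeated simulated trials:

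- ANCOVA of available T2 values: 11.0
- analysis that also uses T1: 10.0

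The overstatement is 11.0 − 10 = 1.0 point (10%). It comes from ignoring T1 values that the trial would hold. Its size depends on the assumed correlations and on which patients are lost.

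**5. Loss with no post-baseline value.** Assumed inputs: 3 of 18 real-arm patients have T0 only and would have had no benefit, and the other 15 benefit by 10. The effect over all randomized patients is 10 × 15/18 = 8.3. A simulation of this case (36 patients, SD 10, T0–T1 correlation 0.6) gave:

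- full data: 8.3
- available-case ANCOVA: 10.0
- ANCOVA after imputation under missing at random: 10.0

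More generally, if a fraction m is missing and has no effect, the all-randomized effect is 10 × (1 − m): 9.5, 9.0 and 8.5 at 5%, 10% and 15%. If values are missing at random given arm and baseline, the bias is about 0.

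**The case against.** The best defence is the retention provision. Patients who stop training or withdraw are asked to keep attending, and those who do are analysed as randomized. That is treatment policy, and it is a fair reading of including the drop-outs. This stands, and it limits the point in two ways. A reader might infer that the primary result is a completers estimate. The documents do not support that: the ANCOVA selects on having a value at the visit, not on finishing the training. A reader might also infer that the all-randomized statement is simply false. It would be true if every patient gave a value, and the full protocol and SAP, which are not shown, may hold an imputation rule.

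A second defence is that a baseline-adjusted ANCOVA with a likelihood-based sensitivity model is an acceptable pairing for a small proof-of-concept trial, that the mixed model already yields T1 and T2 contrasts, and that the evaluable number is a power allowance and not a definition of the analysis set. The pairing is indeed acceptable. What it does not support is the label put on the primary result.

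A third is that the 8.3 against 10 contrast puts every loss in one arm with no benefit. The documents give no drop-out by arm. The tempting inference that a repeated-measures model or imputation would correct that gap is also wrong: step 5 shows both analyses at 10.0. A patient with T0 only tells such a model almost nothing about the arm effect.

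**Conclusion.** The conflict holds in limited form. As the article stands, both confirmatory ANCOVAs are available-case analyses, and the promise to evaluate every randomized patient is not met once a DextQ-24 value is missing at that visit. The planned sensitivity model closes only part of the gap.

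The avoidable part is mainly at T2, where the confirmatory model ignores the T1 values of patients lost later. It is about 1 point on a 10-point effect in one illustration that rests on assumed correlations and an assumed pattern of loss. With losses unrelated to response it is about zero. Bias from patients with no post-baseline value who left for lack of benefit could be of similar or larger size (10 − 8.3 = 1.7 points in the assumed case), but no analysis under missing at random removes it.

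This should be fixed before analysis. It does not undermine the design.

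**What to change.** Make a repeated-measures model confirmatory, by adapting the mixed model already planned: T0, T1 and T2 DextQ-24 as outcomes, one common T0 mean for both arms, arm-by-visit effects and an unstructured covariance. An alternative is to keep the ANCOVA but run it on all randomized patients after multiple imputation that uses T0 and T1. Either way:

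- keep the T1-then-T2 testing order, and keep the available-case ANCOVA as supportive
- state the missing-at-random assumption
- add a simple missing-not-at-random sensitivity analysis, for example delta-adjusted imputation, as this is what addresses patients with T0 only
- report the numbers analysed by arm at T1 and T2

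If the ANCOVA stays confirmatory without imputation, reword the all-randomized sentence to say that patients are analysed as randomized and that the primary analysis uses available cases.

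The cost is analysis wording and some programming, with no new patients or data. With complete data the result would be practically the same as the ANCOVA. The price is an explicit assumption about missing data, which the present plan leaves unstated.

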## Discussion

Dexterity related difficulties during the performance of several ADL are frequently reported in PD, leading to reduced QoL (1–3, 7). Specific dexterity trainings have shown short, (6, 12, 14) but no long-term effects (7). The present study choses an innovative multimodal therapeutical approach, not done before, by using a VBT intervention using two types of devices (GripAble and LMC™), each having its own focus. The GripAble games chosen herein, focus on training train hand/finger pinch grip and release, and different hand movements, which are all key elements for good manipulation of objects. The LMC™ training focus more on independent finger movements. To further boost the effects on dexterity the VBT training is combined with an facilitatory iTBS over SMA, a cortical region being involved in fine motor control (34, 35).

The present proof-of-concept RCT aims at combining, for the first time, VBT and iTBS targeting SMA. The VBT used herein is an attractive new way to train dexterity in PD (9). The games, delivered by using GripAble and LMC™ in this RCT, provide direct feedback, are fun, motivating, and incorporate several levels of difficulty, all aspects which are important to trigger motor learning in PD (8). By combining this attractive training with iTBS we expect to achieve sustainable long-term benefits in dexterity-related ADL also leading to improved QoL in patients with PD. The reason for choosing iTBS is its shorter application time, therefore clinically being more applicable, and lower stimulation intensities compared with conventional rTMS paradigms, inducing more longer-lasting neural effects (23). Currently, TBS seems to be one of the most powerful neuromodulatory stimulation protocols currently available (23).

The total dosage of the present study is 405 min of combined iTBS-VBT training (45 min, three times a week, 3 weeks), representing a short but intensive training. Previous studies using a similar amount of rTMS sessions, already suggested longer lasting behavorial effects, even up to 3 months (53, 54). We assume that a 3-week combined iTBS-VBT training will be enough to achieve both short as well as long-term effects. Furthermore, due to the short training period, it has the potential to be easily implemented in the daily routine of a neurorehabilitation center and at home.

Some limitations have to be mentioned which might occur during the trial. These could be related to the technical devices used in the VBT. The developers of GripAble (see for acknowledgments) are continuously doing efforts to upgrade their system, also by developing new games, potentially interesting for the present trial. However, to avoid contamination of training effects, we will not implement these new games. The long-term follow-up (12 weeks after training) might be a challenge for some PD patients, and may lead to some drop-outs. However, we expect no drop-out rate exceeding 10%, as shown in our previous RCT with a similar design (7).

In summary, the present project aims to investigate, for the first time, the effectiveness of a combined iTBS-VBT 3-week intervention in PD. Its short and long-term benefits will be evaluated. By using iTBS before VBT we expect to further strengthen the VBT effects, also to achieve sustainable long-term effects. The improved dexterity in both the short and long term, will lead to improved ADL and QoL in patients with PD.

## Data Availability Statement

The original contributions presented in the study are included in the article/supplementary material, further inquiries can be directed to the corresponding author/s.

## Ethics Statement

The studies involving human participants were reviewed and approved by Ethics Committee for Northwest and Central Switzerland (EKNZ), Switzerland 2019-00433. The patients/participants provided their written informed consent to participate in this study.

